## Abstract

**Background:**

With the expected increase in the number of people needing care and the increasing shortage of skilled care workers, new care concepts are required. Therefore, digital assistive technologies (DATs), especially robotics, can improve the situation of people with different needs and create opportunities for participation. For a human-technology interaction to have a high level of usability, DAT’s meaningfulness and effectiveness must be accessible to end users. Significant barriers to the use of DATs in health care are the lack of controllability and adaptivity, as well as control functions that are too complex.

**Objective:**

The objective of this paper is to develop an interaction and control platform that is understandable to a layperson and has a programming interface for DAT interactions. The innovation consists of the expansion of usage and interaction options for carers of existing DAT in a more individual manner. This is to be achieved by combining modern interactive media, a modular software architecture, and already available DAT.

**Methods:**

The project is planned as a mixed methods study with a longitudinal design, with multiple user involvements and measurement times in collaboration with 3 care facilities in Germany. When assessing technologies, the satisfaction of the basic human needs of competence, connection, and autonomy plays an important role in the actual use of the technology. These needs can be measured in the form of usability (System Usability Scale), intention to use (Technology Usage Inventory), and satisfaction with the carers’ needs (Technology-Based Experience of Need Satisfaction). In the qualitative assessment, user experience is recorded using the think-aloud method and focus groups in order to obtain information about potential improvements of the platform.

**Results:**

The EduXBot (Educational Exploration Robot Application Platform) project was initiated in January 2023 and is scheduled to conclude in December 2025, at which point the project’s final results are expected to be available. The initial results were attained in the summer of 2024 when the final concept for the platform prototype was developed. In November 2024, an initial prototype of a functional platform for the simplified interaction and control of DAT was evaluated.

**Conclusions:**

It is expected that the open DAT system architecture enables caregivers without any previous technical knowledge to assemble their individual DAT functional portfolio. The results of the project will provide low-threshold access to interaction options for existing DAT as well as expand the usage of such technologies in an individual and patient-centered way.

**Trial Registration:**

Deutsches Register Klinischer Studien DRKS00034195; https://drks.de/search/de/trial/DRKS00034195

**International Registered Report Identifier (IRRID):**

DERR1-10.2196/63089

## Introduction

Digital assistive technologies (DATs) have long been discussed as a way to address pressing health care challenges. On the one hand, these challenges are related to the aging of society and the associated increasing need for care services. On the other hand, the acute and future shortage of nurses makes it difficult to provide care for older adults and those who are sick [1-3]. The digital transformation of health care and the use of DAT could be an opportunity to address these challenges [4]. As the health care system in Germany is under pressure to respond to increasing care needs, one measure is to promote the digital transformation of the health care system [5-7]. However, preliminary work shows that DAT, such as mobile apps, telemedicine systems, and robotics, have not yet been implemented in care processes as sustainably as expected [8,9]. However, when used correctly, DAT can provide opportunities to reduce the burden on caregivers [10-13].

The term assistive technology is a generic term for assistive, adaptive, and rehabilitative devices, which, according to the World Health Organization [14], includes all assistive devices, such as crutches, bedpans, or wheelchairs. For the purposes of this study, the term is expanded to include digital technologies such as augmented or virtual reality technologies or robotic systems. A generally valid definition of DAT is difficult to formulate, however, because DAT can develop potential in different areas [15-17], the effects of which would then have to be demonstrated in a specific application.

Nursing can be described as a complex situation in which the patient must be approached individually and according to the situation. The advent of DAT presents a challenge to health care professionals, who must adapt these technologies to the diverse and individual needs of the patients they care for and integrate them into care processes that must be planned individually. Thanks to their training and professional experience, professional nurses are able to quickly understand these complex situations and make appropriate decisions. It is difficult for nurses to imagine that an algorithm-based system can learn their rules and principles and have the flexibility to know when to modify those rules or not apply them at all. Apart from this, nurses recognize that DAT could reduce the error rate for routine tasks that require high concentration, such as medication preparation or documentation [18].

In addition, ethical concerns play an important role in nurses’ reluctance to use DAT. An aspect of the discussion is the change in the workflow that occurs with the integration of DAT. Nurses fear that the logic of the devices, which is different from their own, will cause additional stress or even make them feel influenced by others. Nurses also fear losing their jobs as technology takes over their activities. Last but not least, there is a fear of losing interpersonal contacts. A change in the psychosocial component of nursing work goes hand in hand with a reduction in the attractiveness of the profession for nurses and should, therefore, be avoided [18,19].

Previous work shows that technology development research has been approached from a technology-centered perspective. Reference to user interests is often only made in the context of raising awareness among target groups, identifying needs in the testing phase, or for a finished technology [20-22]. Participatory design approaches such as cocreation are a solution to foster usability and user acceptance. Cocreation is defined as a collaborative approach that involves end users and relevant stakeholders in all phases of a project [23]. Early involvement of end users can increase acceptance and have a positive impact on patient satisfaction and quality of care [24,25]. In addition, cocreation can increase the successful implementation of evidence-based interventions and policies through equal and deep involvement of end users [26,27].

In order for DAT to unfold its potential, it is necessary, on the one hand, to provide services that are tailored to the respective functional limitations of those in need of care so that the use of DAT can be planned and problem oriented [28,29]. This means that nurses also play a crucial role in the widespread use of DAT. According to a study by the Bertelsmann Foundation, the acquisition of knowledge about existing technical systems is a prerequisite for the use of DAT in care settings, as is the development of application skills on the part of nursing staff [30]. Preliminary work also shows that application knowledge and skills, as well as the opportunity to use DAT in relation to care problems, are beneficial for nurses’ willingness to use DAT [31-34].

To fill this research gap, the EduXBot (Educational Exploration Robot Application Platform) project aims to develop and evaluate a technology-based interaction platform with a reduced complexity control interface as part of a cocreative, exploratory approach to facilitate the control of existing DAT by caregivers. The goal is to provide formal caregivers with a simplified way to use DAT to support caregiving. The aim of this feasibility study is to investigate to what extent a prototype for simplified control of already available DAT changes the willingness of nurses to use them in the nursing process. The collaborative project brings together developers from the field of technology research, nursing scientists, and business partners from the fields of project management for digital work environments and the development of digital formats for knowledge transfer. The cocreative nature of the project means that in addition to the scientific project staff, nurses will be involved as end users in every phase of the project. This ensures that the project goals are better achieved in terms of user needs and technical feasibility.

## Methods

### Conceptual Framework

The project aims at the participatory development and evaluation of a platform to promote the applicability of DAT in care settings. A feasibility study with a longitudinal design will be conducted based on a mixed methods approach. The main goal of the platform is a simplified application of DAT to support care processes. The development will be carried out in a participatory manner as a user-centered design (UCD) based on the suggestions of the “Motivation, Engagement, Thriving in User Experience” (METUX) model [35], which takes into account the expectations and experiences of the end users and promotes the intention to use (ITU) and thus the usability, relevance, and creativity of the platform, thus concretizing the overall implementation concept.

In practical implementation, the project is based on the theoretical model of UCD and follows the suggestions of the cocreative design cycle [36]. The UCD approach is used to cocreatively develop a more needs-based and more tailored end product based on the nurses’ expert knowledge and to take possible consequences of implementation into account [36-38]. Positive effects are promised in terms of improving the identified outcomes as well as greater usability and user acceptance of technical products [39,40]. The cocreative design cycle is the process by which all relevant stakeholders are involved in the design and development of technologies. End users are actively involved in the design and development of solutions that meet their challenges. The result of the process is innovative and creative solutions that are useful, effective, and user centered, thereby promoting their actual use [41].

The user-centered and cocreative approach used in this study integrates 3 cycles (Figure 1) that incorporate the realities of end users (relevance cycle) and the scientific knowledge base (rigor cycle) into the development of technical products (design cycle) [42-45]. With this chosen approach, it is better possible to theorize, collect, and ultimately practically map the requirements for the technologies used in the study in the sense of determining needs. At the same time, collaboration between scientists and end users is more possible. Furthermore, end users can be more actively involved in product evaluation over the course of the test cycle. This ensures the functionality and, ultimately, the success in terms of improved applicability of a platform.

In the first step (relevance cycle), needs, functionalities, and application scenarios of and with nurses as end users are identified through focus groups. The selection of the DAT used in the project is based on the conditions of the cooperating institutions and the needs of the nursing staff. In order to clearly define nursing problems in the context of the learning scenarios, the concept of nursing need (see §14 Sozialgesetzbuch XI [Social Codebook XI]) is used. Based on this concept, DATs are selected that are already available and ready for use. These should cover a wide range and variety of technologies (from a mobile telepresence system to a complex humanoid robot).

Based on the results of this procedure, concrete scenarios will be outlined that are necessary for the implementation of a first demonstration model of the platform. In the next steps, the prototypes will be developed in 4 iterations with respect to usability, user acceptance, and satisfaction of basic psychological needs of the end users until the first prototype can be tested under simulated and real conditions in the facilities. The development of the prototype takes place schematically in 4 steps (Figure 2).

**Figure 1 figure1:**
[figure not shown]
User-centered and cocreative design of the platform development (according to Farao et al [36]). DAT: digital assistive technology.

**Figure 2 figure2:**
[figure not shown]
The development of the platform takes place in 4 steps. DAT: digital assistive technology.

### Technical Description

The innovation of the project does not lie in the development of new DAT per se but in the creation of extended usage and interaction possibilities for already available DAT. By combining modern interactive media and a modular software architecture, EduXBot aims to achieve the next level of DAT use in the care of people with disabilities, forced isolation, or restricted movement. The DAT should also promote an individual, programmable user interface for caregivers in an easier way to better meet the needs of those in need of care. EduXBot represents an experience and learning platform with 4 main functions (Figure 3): (1) programming (simplest type of programming), (2) community platform (“widget platform,” users can share their apps), (3) using and controlling (easy way to interact, control, and use the DAT), and (4) augmented reality (AR) experience (experience and learn through AR content).

The multipart concept for using the platform then allows people with diverse previous technological knowledge to use DAT. That means EduXBot leads to the development of a layperson’s iteration with the intention of human-technology interactions, which is developed in the form of a cocreative process together with the end users. EduXBot does not focus on the development of new care technologies that replace caregivers per se but rather on creating supportive interaction options that could relieve the burden on caregivers. The flexible and open system architecture of the platform supports this by keeping different DAT, sensors, and interaction systems available for different usage options. With the help of the development of low-threshold digital access options through an intuitive user interface with community and operator connections, informal support and supply networks are also strengthened as they enable participation in social networks.

**Figure 3 figure3:**
[figure not shown]
The 4 main functions of the EduXBot platform. AR: augmented reality.

### Study Design

#### Overview

EduXBot is a longitudinal feasibility study based on a mixed methods approach. The mixed methods approach combines aspects of quantitative and qualitative research in order to examine the research topic from different perspectives and to answer questions that could not be answered by a purely quantitative or purely qualitative study [46]. The researchers initiated the study with a quantitative phase, which was followed by a second qualitative phase that provided a more in-depth explanation of the initial results [47].

A total of 3 care institutions (1 inpatient, 1 outpatient, and 1 life-sustaining) that support people in their health care and daily life were recruited to participate in the project. The institutions were contacted as partner institutions in previous DAT research projects and agreed to participate in this project. Therefore, it can be assumed that the participating nurses are generally aware of the topic of DAT in nursing. The facility managers will be informed in detail about the project and will be asked to act as gatekeepers to motivate the nurses and relatives in their facility to participate in the research project.

Participants are invited to take part in the study as test subjects by the facilities with which they are affiliated. The participants are as varied as possible in terms of age, gender, length of professional experience, and so forth [48]. The inclusion of nurses from diverse backgrounds within the facilities serves to enhance the heterogeneity of the study sample, thereby contributing to the study’s overall value. It should be noted that some participants may be unable to commit to the study due to scheduling conflicts or other commitments, while others may choose to withdraw (Textbox 1). It is essential to emphasize that no financial compensation is provided for participation in the study. However, those who elect to take part receive certain benefits, including complimentary refreshments during the workshop sessions and, upon request, recognition of their institution and name in the project acknowledgments.

Description of the inclusion and exclusion criteria of the participants.
**Inclusion criteria:**
The participants could be nursesThe participants could be the support staffCurrently in a facility that belongs to the project’s practice partnerSufficient in written and spoken German
**Exclusion criteria:**
Those who do not want to participate at the beginning or withdraw later

In the context of research involving human participants, it is imperative to consider pragmatic factors such as financial resources and the maximum feasible number of participants in accordance with the guidelines for designing and evaluating feasibility pilot studies [49]. According to the guideline, achieving saturation in a study occurs at 30 participants. Statistical principles suggest that 30 individuals are sufficient to ensure the normality of the sample size [50,51]. Therefore, the objective is to recruit a minimum of 30 caregivers. It is important to acknowledge that the implementation of blinding is not a viable option in this context, as the participants are required to actively engage with the technologies under study.

The primary objective of this study is to design the human-technology interaction between the platform and users in a manner that ensures a high level of usability for all users. The objective is to assess whether the accessible platform alters the intended use of DAT by offering a simplified application option for caregivers. This inquiry seeks to ascertain the potential for DAT to be integrated as a supplementary resource in the planning of individual care processes. The central question guiding this study is whether the EduXBot platform offers an interface that enhances the autonomy of caregivers’ DAT use. The objective is to enhance usability by a minimum of one level over the course of the study. The primary objective is to ascertain the extent to which the platform affects the usability of DAT (System Usability Scale [SUS]), the intention to use it (Technology Usage Inventory [TUI]), and the satisfaction of caregivers’ needs through technology (Technology-Based Experience of Need Satisfaction [TENS]).

The secondary objective is to develop a multilevel benefit concept for EduXBot. This will provide caregivers with different affinities for electronic media, as well as different levels of technical expertise, and will offer them windows of opportunity to use and experience the platform. The objective is to conduct a direct assessment of the EduXBot platform by the participating nurses and to evaluate the platform with the aim of continuously improving the content and application options of the platform. A secondary objective is to record user satisfaction in order to obtain information on potential improvements to the platform through the analysis of structured feedback. The collection of qualitative data will be facilitated through the implementation of think-aloud (TA) and focus group methods. The aim is to empower caregivers to articulate their subjective experiences and perceptions regarding the utilization of EduXBot in an unstructured manner.

The third objective is the long-term evaluation of the EduXBot platform, encompassing not only its readiness for implementation but also its potential for long-term integration, utilization, and management of DAT. A further objective is to examine the interrelationship between the perceived ITU, usability, and user acceptance of the platform, which is currently being developed for the application. The tertiary target variable is the long-term willingness to use DAT in a sustainable manner and to integrate the digital assistive support offering into the existing care provision framework.

The measurement times are based on the development process shown in Figure 2. This allows changes in improving ITU to be measured. Since there are different versions with different application scenarios, especially at TUI, Table 1 is intended to provide an overview of the measurement times and evaluation methods used.

**Table 1 table1:** Different questionnaires are used at different measurement times.

Measurement time	Evaluation method
T0: Identification of functionalities and application scenarios	TUI^a^ original questionnaire (pre-post version) Focus group
T1: Development of the prototypes	TUI II parallel questionnaire (complete version) Focus group
T2: Piloting and testing	TUI II parallel questionnaire (complete version) SUS^b^ TENS-Interface^c^ Focus group
T3: Adjustments	TUI II parallel questionnaire (complete version) SUS TENS-Interface Focus group
T4: Use	TUI II parallel questionnaire (complete version) SUS TENS-Interface Focus group

^a^TUI: Technology Usage Inventory.

^b^SUS: System Usability Scale.

^c^TENS-Interface: Technology-Based Experience of Need Satisfaction–Interface.

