## Discussion

### Principal Findings

The objective of this study is to design the human-technology interaction between an interaction and control platform and nurses in such a way that a process is created that ensures the high usability of DAT in nursing care. The central question guiding this study is whether the low-threshold platform changes the intended use of DAT through the simplified application options for nurses in order to integrate DAT as possible supplementary resources into individual nursing process planning. The objective is to assess whether the platform offers an interface that enhances the autonomy of nurses in using DAT. The evaluation will yield both quantitative and qualitative data, providing insights into the requirements of nurses as end users of DAT. The objective is to enhance the usability of the platform by at least one level over the course of the study.

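### SUS and TENS-Interface start at T2, so they can show change between platform versions but not the platform's effect on DAT usability or need satisfaction

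*Protocol article*

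**What the plan says.** The Overview under Study Design states: "The primary objective is to ascertain the extent to which the platform affects the usability of DAT (System Usability Scale [SUS"]). The same sentence goes on to intention to use (TUI) and to "the satisfaction of caregivers’ needs through technology (Technology-Based Experience of Need Satisfaction [TENS"]).

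Table 1 then sets the schedule:

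- T0: the TUI in its "original questionnaire (pre-post version) Focus group".
- T1, labelled "T1: Development of the prototypes": "TUI II parallel questionnaire (complete version) Focus group".
- T2, the piloting stage: "TUI II parallel questionnaire (complete version) SUS^b^ TENS-Interface^c^ Focus group".
- T3 and T4: "TUI II parallel questionnaire (complete version) SUS TENS-Interface Focus group".

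The Discussion (Principal Findings) gives the success target: "The objective is to enhance the usability of the platform by at least one level over the course of the study". The Overview has the same one-level target but does not say whose usability is meant. The Quantitative Evaluation section describes a pre-platform baseline for the TUI only, and ties its analysis of differences between measurement times to intention to use.

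**The concern.** To learn how far a platform affects the usability of DAT, one needs usability with the platform and usability without it. Without a parallel group, the second value has to come from the same caregivers before the platform arrives. Table 1 does not collect it for SUS or TENS-Interface.

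At stake is the interpretation of two of the three measures named in the primary objective. The prototype is developed in iterations, so scores may rise from T2 to T4 because early faults are repaired. That is a proper formative result. It does not show that caregivers find DAT easier to use, or their needs better met, than with the devices' existing controls.

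**Working it through.** No sample-size or error-rate figure bears on this point. The check sets the schedule against the objective.

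**Step 1. Count administrations (Table 1).**

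| Instrument | T0 | T1 | T2 | T3 | T4 | Total | At T0 |
|---|---|---|---|---|---|---|---|
| TUI | yes | yes | yes | yes | yes | 5 | 1 |
| SUS | no | no | yes | yes | yes | 3 | 0 |
| TENS-Interface | no | no | yes | yes | yes | 3 | 0 |

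**Step 2. List the within-person contrasts.** Three waves give 3 × 2 / 2 = 3 pairs: T3 − T2, T4 − T2 and T4 − T3. For SUS and for TENS-Interface, 0 of the 3 has a pre-platform member. For the TUI, each of T1 to T4 can be set against T0, which gives 4 such contrasts.

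**Step 3. Identify what is rated from T2 on.** Table 1 does not name the object. Three places point to the prototype: T2 is the piloting and testing stage, the Conceptual Framework has the first prototype tested in the facilities once development iterations are done, and the Discussion words the target as usability of the platform. The inference is strong, but it remains an inference.

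**Step 4. Look for another reference.** No control group is described. The Quantitative Evaluation section gives an average SUS score of 68 across studies. That is an external benchmark, not a value for these caregivers using these devices without the platform.

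**Step 5. Show why the missing value matters.** Let B be the SUS score for DAT under its own controls. The plan observes T4 − T2. The effect on DAT usability is T4 − B, and B is not measured. The following scores are assumed for illustration only: T2 = 55 and T4 = 69.

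- Observed change: 69 − 55 = +14, from the Ok band to the Good band of Table 4.
- If B = 50 (bottom of the Ok band): 69 − 50 = +19.
- If B = 68 (the external average): 69 − 68 = +1.
- If B = 70: 69 − 70 = −1.
- If B = 89 (top of the Excellent band): 69 − 89 = −20.

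The same observed gain fits a clear benefit, no difference or a clear loss. The range illustrates what is not identified; it does not predict a result.

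**The case against.** The strongest reply is that one sentence is being read alone. The Overview first describes the primary objective as designing the interaction between platform and users for high usability, which concerns the platform, and T2 to T4 can address that. The Discussion says the same. This largely stands. A reader might infer that the Discussion switches the target, but the Overview already mixes platform usability with DAT usability. The sentence naming SUS and TENS as measures of an effect on DAT and on needs is still there, and the schedule cannot answer it.

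Second, the main question in the Quantitative Evaluation section is change in intention to use, and the TUI has a T0 baseline. This stands in full. A reader might infer that the study as a whole lacks a baseline; the documents do not support that.

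Third, nothing in the article says that a gain from T2 to T4 will be reported as an improvement in DAT usability, and the external average and adjective bands would make a poor absolute score visible. This is also fair. The risk comes from the wording of the objective, not from a declared reporting plan.

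Fourth, this is an uncontrolled, co-creative feasibility study with descriptive analysis. That lowers the severity. It does not remove the mismatch, because the article itself prints both the objective and the full instrument schedule, and no separate analysis plan can create a value that is not collected.

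**Conclusion.** The point holds in a limited form, at moderate severity. For SUS and TENS-Interface, none of the three available contrasts includes DAT without the platform, so the stated objective for these two measures is not answerable from the schedule. What they can show is change between platform versions from T2 to T4. Intention to use is unaffected.

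The conclusion rests on Table 1 being the complete schedule and on the prototype being what is rated from T2 on. The documents do not support the stronger claim that the platform will be shown to help when it does not: the value that would decide this is unknown, and the scores used above are assumed.

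**What to change.** **Restate the objective.** In the Overview under Study Design and in the Discussion (Principal Findings), word the SUS and TENS objective, and the one-level usability target, as change in the platform's usability and in need satisfaction from T2 to T4. State that no conclusion will be drawn from SUS or TENS-Interface that the platform improves DAT usability or need satisfaction relative to DAT without it.

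**Supportive evidence.** The TUI Usability scale from T0 may be reported alongside, assuming the T0 form carries it (only the immersion scale is said to be excluded). It needs a caveat. T0 uses the original form and later waves use TUI II, and the Quantitative Evaluation section allows item wording to be adapted to the technology, so the rated object may also differ. TENS-Interface has no such substitute.

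**Not proposed.** Asking participants at later waves to rate the same DAT under its own controls would not restore a baseline. Those ratings would follow exposure to the platform, would be open to order and contrast effects, and would need extra sessions operating each device. Collecting SUS and TENS-Interface at T0 is no longer possible: the Results section dates the first prototype evaluation to November 2024.

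**Cost.** The restatement changes wording only, with no new data collection. The downside is a narrower claim on usability and need satisfaction.
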